## Background

Over the last few years, the epidemics of noncommunicable diseases and the need for cost-containment^1^ are triggering factors for a profound transformation of the way we approach delivery of care for chronic patients. In this new scenario, conventional disease-oriented approaches, centered on the management of clinical episodes, are being replaced by patient-centered integrated care services,^2^ as promoted by the World Health Organization.^3^

Lessons learnt from deployment experiences^4, 5^ following patient-centered approaches are being disseminated as good practices.^6^ However, there are several factors that need further attention, such as the need for further assessment of implementation strategies in real-world scenarios and the lack of transferability from progress achieved in disease-oriented integrated care to management of complex chronic patients (CCP).^5, 7^ Likewise, efficacy achieved in integrated care interventions, assessed through randomized controlled trials,^8–11^ may not translate into effectiveness at health system level.^12^

In addition, poor comparability among experiences on management of multimorbidity emerges as an important hurdle for the adoption of integrated care. In this regard, the lack of an operational definition for CCP is not a negligible factor, as it clearly limits an appropriate service workflow design, which, in turn, precludes both evaluation and comparability of reported experiences.^5–7^

The term CCP is usually applied to subjects with heterogeneous conditions that may depict at least one of the following three traits: (i) need for management by several specialists from different disciplines generating high use of healthcare resources; (ii) frailty,^13^ requiring additional support either due to functional decline, social deficits, and/or transient situations like post-hospital discharge^14–16^; or, (iii) need for highly specialized care with home-based technological support.^4^ Moreover, CCP often show a dynamic evolution over time in terms of both health risk and care requirements,^6^ such that their management requires a balance between planned (predefined and repeatable) and unplanned processes (depending on evolving circumstances and ad-hoc decisions).

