The CCP protocol relies on the hypothesis that implementation of (i) structured, but flexible service workflows, that is, a collaborative and adaptive case management approach^17^ and (ii) enhanced patient health risk assessment and stratification can overcome current limitations of multimorbidity management. The protocol for management of CCP aims to assess the study hypothesis through the evaluation of the regional deployment of two existing integrated care interventions (i.e., implementation studies) described below. It is of note that the protocol evaluation will also include a population-based analysis of CCP management.

The two implementation studies have a quasi-experimental design. That is, a nonrandomized intervention group (integrated care) is compared to a control group (usual care) using propensity score methods^18^ wherein age, gender, and population-based health risk assessment are the main variables to be used for adjustment. The Catalan population-based health risk assessment tool (GMA, Adjusted Morbidity Groups)^19, 20^ will be used for health risk scoring purposes. The protocol evaluation follows a Triple Aim approach^21, 22^ considering predefined outcome variables for (i) health and well-being, (ii) experience with care, and (iii) costs. Assessment will be carried out combining empirical questionnaire data collection, information from electronic medical records, and registry data. The main study outcome will be twofold: (i) demonstration of cost-effectiveness of the interventions; and, (ii) identification of factors that modulate success of large-scale deployment. A post-hoc statistical power analyses for assessment of the main protocol outcomes will be done.

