**Fig. 5 Fig5:**
[figure not shown]
Stratification of the Catalan population (2014) using the GMA. Previously published in Dueñas-Espín I et al., BMJ Open. 2016 Apr 15;6(4) as part of the online supplementary material (Supplementary Figure 2S). The third and fourth columns depict rates of mortality and hospital admissions, respectively. The fifth column indicates the cost per inhabitant per year expressed in € and the last column refers the percentage of total healthcare expenditure by risk strata. It is of note that the closer the patient is to the tip of the pyramid, the higher are mortality, risk of hospital admission, and healthcare expenses. *Green color* (*bottom*) indicates healthy status, whereas *red* (*tip*) corresponds to maximum risk of admissions and highest mortality risk

Prospective assessment of both practicalities and added value of the use of GMA scoring for enhanced clinical risk prediction and stratification, as reported in detail elsewhere,^19^ has been successfully completed in Catalonia for the entire population of patients with Chronic Obstructive Pulmonary Disease (unpublished). This approach will be incorporated in the implementation studies undertaken into the current CCP protocol aiming at enhancing risk prediction in the clinical scenario.

The GMA tool predicts individual patient risk based on multimorbidity information gathered from the Catalan Health Surveillance System described below. The rationale behind the use of GMA, against alternative health risk assessment tools, is that it complies with four main recommended criteria^19^; that is, (i) a population health approach (using the entire source population of 7.5 million inhabitants of the region); (ii) publicly owned without licensing constraints; (iii) open-source computational algorithms; and, (iv) the GMA morbidity grouper relies on statistical criteria, as opposed to other tools that include expert-based coefficients, thus facilitating quick transferability to other territories, as recently shown in Spain wherein GMA risk assessment is used in 38 million inhabitants.

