### Assessment of healthcare value generation

The evaluation strategy (see Supplementary Methods for further details) has a threefold aim: (i) identification of factors that modulate large-scale deployment of the two implementation studies in the three sites; (ii) assessment of cost-effectiveness of the intervention for enhanced community-based management of CCP; and (iii) evaluation of the added value of the technological support for integrated care management of patients under LTOT. To this end, we will use implementation research tools^33, 34^ organized within the frame of the Model for ASsesment of Telemedicine applications.^35^ As alluded to above, the two implementation studies have a quasiexperimental design wherein integrated care (intervention) will be compared to usual care (control) with age, gender, and GMA scoring as main matching variables. Moreover, a population-based analysis of CCP management using registry data from the Catalan Health Surveillance System (CHSS) (Supplementary Fig. 1) will be carried out assessing separately intervention and control areas in each of the three sites.

Predefined outcome variables (Table 1) will include the eleven indicators recommended by the Spanish Health System^36^ for assessment of four care coordination categories of variables. At the end of the study, we will propose Key Performance Indicators, selected among those used in the regional deployment phase, to be considered for population-based assessment of integrated care interventions for CCP beyond the lifespan of the study.

**Table 1 Tab1:** Predefined outcome variables for evaluation purposes selected with a “Triple Aim” approach

Triple Aim	Outcome	Data source and Instrument
Health and well-being	Sociodemographics	Catalan Health Surveillance System and Electronic Medical Records
	Multimorbidities	Catalan Health Surveillance System and Electronic Medical Records
	Patient Clinical Data	Electronic Medical Records
	Health-related quality of life	SF-36 questionnaire^37^
	Therapeutic plan (Pharmacological/Others)	Catalan Health Surveillance System and Electronic Medical Records
	Intermediate outcomes (see costs):	Catalan Health Surveillance System
	• Emergency department visits	
	• General practitioner visits	
	• Cumulative days per year admitted in hospital	
	• Multiple drugs’ prescription	
	• Potentially avoidable hospitalizations	
	• Hospital readmissions	
	• Needs for social support	

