^(2)^ The Catalan Health Surveillance System registries (Supplementary Figure 1) allow allocation of healthcare expenditure to each patient through the Personal Health Identification Number, which facilitates analysis of total healthcare expenditure in complex patients

Data for evaluation purposes, for both implementation studies and population-based analysis (Table 1 and Supplementary Fig. 1), will be obtained from (i) Electronic Medical Records; (ii) the CHSS; and, (iii) Standardized questionnaires selected with a “Triple Aim” approach,^21, 22^ this is, considering predefined outcome variables for (i) health and well-being, (ii) experience with care, and (iii) costs.

The CHSS (Supplementary Fig. 1) includes updated registries from Primary Care, Hospital-related events (hospitalization, emergency room, and specialized outpatient visits), Pharmacy, Mental Health, Sociosanitary services, respiratory therapies, dialysis, outpatient rehabilitation, nonurgent health transport, outpatient minor surgery, home hospitalization and implants since 2011. It allows analyses on use of healthcare resources, pharmacy consumption, and prevalence of key disorders. The CHSS also feeds the population-based health risk assessment tool known, GMA, that is used to elaborate the health risk strata pyramid of the general population of Catalonia,^19, 20^ which is periodically updated on a 6-month basis. The CHSS allows allocation of healthcare expenditure, including pharmacy, to each patient through the Personal Health Identification Number, which facilitates analysis of total healthcare expenditure in complex patients.

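### The patient's own pre-entry cost and hospital use are not named among the main matching variables, although the registry holds them and they are the earlier values of the outcomes: a cheap improvement

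*Protocol article*

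**What the plan says.** The Background describes the design of both implementation studies: "a nonrandomized intervention group (integrated care) is compared to a control group (usual care) using propensity score methods". It then states that "age, gender, and population-based health risk assessment are the main variables to be used for adjustment". The Methods section on assessment of healthcare value generation repeats the choice, "with age, gender, and GMA scoring as main matching variables", and points elsewhere for the rest of the evaluation: "see Supplementary Methods for further details".

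On the score itself, the section on enhanced health risk assessment says: "The GMA tool predicts individual patient risk based on multimorbidity information gathered from the Catalan Health Surveillance System". The caption of Fig. 5 adds that mortality, admission risk and expenditure all rise towards the top GMA strata.

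Table 1 lists total cost, admissions, days in hospital, readmissions and emergency visits as outcomes, most of them from CHSS. The same section says that CHSS can attribute expenditure to each individual. Its list of registries ends "outpatient minor surgery, home hospitalization and implants since 2011", which I read as dating the whole list. The first Barcelona-Esquerra patients entered in January 2017, so several years of history precede entry.

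No section of the article names a patient's own earlier cost, admissions, bed-days or emergency visits as a matching or adjustment variable.

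**The concern.** In a comparison without randomisation, the earlier value of the outcome is usually one of the strongest confounders on hand and one of the best predictors. Here it is already in the registry that supplies the outcomes, but it is absent from the variables the article ranks first.

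The article gives its own reasons to expect prior use to matter. Its first trait of a complex chronic patient is the "need for management by several specialists from different disciplines generating high use of healthcare resources"; the second is frailty, including functional decline and social deficits. Age and gender do not measure these, and the text says only that GMA is built on multimorbidity information.

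Entry to the complex chronic patient (CCP) intervention is also selective. Patients are recruited straight after discharge, have a LACE index of at least 7, live at home, have a telephone and agree in writing. Two patients alike in age, gender and GMA can differ in these respects.

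At stake is cost-effectiveness, one of the two parts of the main outcome. The bias could run either way: recruiting heavier prior users would make the programme look costlier, and recruiting lighter users would make it look cheaper. A large sample shrinks the standard error but not the bias.

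**Working it through.** The article gives no effect size, SD, significance level, power or control-group size, so there is no stated figure to reproduce. What follows is an illustration.

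**Inputs from the article.** Intervention groups of 3000 (CCP) and 500 (long-term oxygen therapy, LTOT), in the section on implementation studies.

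**Assumptions.** Equal group sizes; outcome SD of 1 given age, gender and GMA; two-sided 5% test. The correlation rho of prior use with the outcome, given age, gender and GMA, is 0.2 to 0.6. The group difference d in prior use left after matching is 0 to 0.2 SD.

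**Standard error.** SE = sqrt(2/n): sqrt(2/3000) = 0.026 and sqrt(2/500) = 0.063.

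**Bias.** Bias = rho × d, from 0 (d = 0) to 0.6 × 0.2 = 0.12 SD. The chance of declaring an ineffective programme different is Φ(bias/SE − 1.96) + Φ(−bias/SE − 1.96):

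| rho | d | Bias (SD) | 3000 per group | 500 per group |
|---|---|---|---|---|
| any | 0 | 0 | 5% | 5% |
| 0.2 | 0.1 | 0.02 | 12% | 6% |
| 0.3 | 0.1 | 0.03 | 21% | 8% |
| 0.3 | 0.2 | 0.06 | 64% | 16% |
| 0.5 | 0.2 | 0.10 | 97% | 35% |
| 0.6 | 0.2 | 0.12 | over 99% | 48% |

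**Variance.** Adjustment multiplies residual variance by 1 − rho²: 0.96 at rho 0.2 and 0.64 at rho 0.6, a cut of 4 to 36%. This equals 1/0.96 = 1.04 to 1/0.64 = 1.56 times the sample. At 80% power the smallest detectable difference, (1.96 + 0.84) × SE, is 0.072 SD at 3000 per group and falls to 0.071 (rho 0.2) or 0.058 (rho 0.6). At 500 per group it is 0.177 SD and falls to 0.174 or 0.142.

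**Cross-check.** A simulation of propensity weighting had a true effect of zero, rho 0.5, selection on prior use of 0.2 per SD on the log-odds scale, and about four controls per intervention patient. Without prior use in the propensity model the mean estimate was 0.097 SD (n = 3000) and 0.099 SD (n = 500), close to 0.5 × 0.2 = 0.10. With it, the estimates were −0.001 and −0.002.

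**The case against.** - **The list is open.** The article calls the three variables *main* both times, and it refers to Supplementary Methods that are not shown. A full covariate list is something an article commonly leaves to such documents. This stands: a reader might infer that prior use is excluded from the analysis, but the text does not say so. What can be said is that prior use is left out of the top rank, twice.
- **No outcome model is stated.** A reader might also infer that only post-entry levels are compared, or that pre-entry differences go unchecked. The article says neither.
- **GMA already carries part of the signal.** Fig. 5 shows cost and admissions rising with stratum, and CHSS feeds the score. This stands too, so it would be wrong to say that GMA holds no information on resource use. But that gradient runs across the whole population, from healthy to highest risk. It does not show how well GMA separates prior use among recently discharged patients or those on oxygen. Taking rho as conditional on GMA allows for this.
- **The size rests on assumed inputs.** This stands. With no leftover imbalance the bias is zero, and the article states only intervention-group sizes.
- **LTOT differs from CCP.** Its listed main outcomes are adequacy of prescription, adherence and community-based management, and no index admission is described. The assessment section attaches cost-effectiveness to CCP, although the Background speaks of the interventions in general. For LTOT the point therefore concerns the CHSS cost and utilisation outcomes only.

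**Conclusion.** The point holds as a cheap improvement. The article twice ranks its adjustment variables, and the pre-entry values of its own cost and utilisation outcomes are not in that rank, although they are available per patient. Residual imbalance is plausible because entry is selective and GMA rests on multimorbidity information.

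The stronger statement, that bias and excess variance do remain in the results, is not supported. Bias needs two things at once: prior use must predict the outcome beyond age, gender and GMA, and the groups must still differ on it after matching. The article gives neither quantity. Under the assumptions above the bias is 0 to 0.12 SD, against standard errors of 0.026 SD (3000 per group) and 0.063 SD (500 per group). The precision gain needs only the first condition and is 4 to 36% of the variance. No figure printed in the article is shown to be wrong.

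**What to change.** 1. For each CHSS cost and utilisation outcome, name the patient's own value over the 12 months before entry as one of the main matching or propensity variables, and also as a covariate in the outcome model. In CCP, leave out the index admission. If the Supplementary Methods already include these values, one sentence saying so is enough.
2. Anchor the window to the same kind of event in both groups: an eligible discharge in CCP, and a common calendar or entry date in LTOT. Otherwise adjusting for prior use can itself bring in regression to the mean.
3. Use baseline SF-36 as a covariate for SF-36 where it is collected.
4. Add a placebo contrast, which should be near zero. Run it on an earlier year that is not in the model, for example months 13 to 24 before entry, or on the pre-entry year in an analysis that omits that year's values. If the same year were both covariate and outcome, the contrast would be zero by construction and show nothing.

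The cost is one more extract from a registry already in use, some wording in the analysis plan and a little more analysis work.

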### Data availability

Data sharing is not applicable to this article as no data sets were generated or analyzed during the current study.
